### Concomitant Medication

All concomitant medications except conventional treatments for ischemic stroke are prohibited. Medications that have been used for the participants’ underlying medical condition for 12 weeks prior to screening that are considered stable and unlikely to affect the interpretation of the results of this study with no change in dosage or dose will be allowed with a note of the reason, as determined by the investigator. Transient symptoms unrelated to stroke, such as cold, flu, dyspepsia, constipation, and concomitant use, will be allowed on a one-time basis at the discretion of the investigator. The use of supplements such as vitamins is not permitted. The use of vitamin K antagonists, direct thrombin inhibitors, factor X inhibitors, and heparin (except for temporary use during percutaneous coronary intervention) that may affect bleeding propensity will be strictly prohibited.

### Sample Size

In previous studies, ischemic stroke recurrence rates of 12.5%-12.8% over 24 months with conventional antiplatelet therapy (aspirin or dipyridamole) [22] and 1.7% over the same period with HH333 [19] were reported. Therefore, the sample size was 106 patients per group and 212 patients in total at 2 years with a control group (P_2_=0.125-0.128), HH333 group (P_1_=0.017), a significance level (α) of 5% and a target power of 80%. Finally, a dropout rate of 10% was considered, resulting in a sample size of 118 patients per group for a total of 236 patients.

### Statistical Analysis

All statistical analyses were two-sided with a 5% significance level. The statistical program SAS (version 9.4 or more, SAS Institute) was used for the analysis. If at any point there are missing values or participants are dropped before the end of the study, the data will be treated as missing data. All data obtained from the participants were analyzed in 3 forms: full analysis set, per-protocol set, and safety set. Efficacy analysis will be conducted using the results of the full analysis set as the main analysis, and a per-protocol set analysis will be conducted separately to evaluate whether there are differences from the full analysis set results. Safety analysis was performed on the safety set and the safety of the study medications was evaluated. The full analysis set includes all data from participants with at least one efficacy assessment at the primary outcome after taking the study medication. The per-protocol set included participants who were eligible for full analysis and successfully completed the study. The safety set included all data from participants who received at least one dose of the study medication.

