**Dropout criteria**
If the researcher determines that it is not appropriate for the study to continue according to the dropout criteria, the researcher may stop the treatment and evaluation and drop the participant. Participants may also drop out of the study at any time of their free will. The dropout criteria were as follows:Found not to meet inclusion or exclusion criteria after screening.Patients or caregivers withdraw consent during the study period.Patients or caregivers request to discontinue the study or refuse treatment during the study.Participants cannot be traced.According to the judgment of the investigator, the patient is no longer able to participate in the study because of adverse events or comorbidities.Study medication compliance <80%.Participation in another clinical trial.Judged by the investigator as unfit to continue the study for any other reason.

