### Exploratory Endpoints: K-NIHSS, mRS, K-mBI, and K-MoCA

The NIHSS is a tool for assessing neurological deficits resulting from stroke developed by the National Institutes of Health [32] and is currently the most widely used tool for stroke severity assessment, with a Korean version validated and used [33]. It comprises 15 questions in 11 checkpoints, each of which is scored on a scale of 0 to 4, with a total score calculated, with higher scores indicating higher severity. The mRS is a tool developed by van Swieten et al to assess the degree of disability in patients with stroke [34] and is currently the most widely used stroke functional assessment scale [35]. It is rated on a scale of 0 to 6, with higher scores indicating more severe impairment. The mBI is a tool to assess independence in activities of daily living after stroke developed by Shah et al [36], and translated with validation in Korean [37]. It contains 10 questions, each rated on a scale of 0 to 5, 0 to 10, or 0 to 15, with a higher total score indicating a lower dependency. The MoCA is a tool that examines cognitive function and was originally developed to identify mild cognitive impairment [38] but is now widely used for cognitive impairment caused by stroke, and the Korean version has been validated and used [39]. It consists of visuospatial and executive (5 points), naming (2 points), attention (6 points), language (3 points), abstraction (2 points), delayed recall (5 points) and orientation (6 points). The perfect score is 30, with a higher total score indicating higher cognitive function. Investigations were conducted during the administration period on days 0 (baseline), 90, 180, 270, 360, 450, 540, 630, and 720.

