#### Analysis of Secondary Efficacy and Exploratory Endpoints

Secondary efficacy endpoints that FSS, FAS, K-PHQ-9 total score change, each pattern identification probability change, and exploratory endpoints K-NIHSS, mRS, K-mBI, K-MoCA total score change are continuous variables, and the average for each measurement, SD, median, minimum value, maximum value will be presented and the difference between the HH333 group and the control group will be tested using repeated measures ANOVA.

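### Scores after dropout are treated as missing with no exception for death or recurrent stroke, which can dilute the exploratory functional comparison by an amount the plan leaves open

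*Protocol article*

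**What the plan says.** All references are to the protocol article.

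- **Missing data (Statistical Analysis).** If "participants are dropped before the end of the study, the data will be treated as missing data". Neither death nor a preceding recurrent stroke is treated separately.
- **Dropout (Textbox 1).** The researcher may end treatment and evaluation together. One listed reason is the investigator's judgment that "the patient is no longer able to participate in the study because of adverse events or comorbidities". Compliance under 80% is another, and the Interventions section repeats it as exclusion at any point. Recurrent stroke is not on the list.
- **Safety Assessments and Monitoring.** Adverse events unrelated to study medication are said not to be grounds for dropout. The same section says that a serious adverse event stops the study, wholly or partly.
- **Schedule (Table 1).** The secondary and exploratory scales are due at day 0 and at each visit from day 90 to day 720, with no stop at recurrence. They may also be done at unscheduled visits.
- **Scales and analysis.** Of the mRS the article says: "It is rated on a scale of 0 to 6, with higher scores indicating more severe impairment". It does not say what level 6 means or how a death is scored. The analysis section says that "exploratory endpoints K-NIHSS, mRS, K-mBI, K-MoCA total score change are continuous variables", tested by repeated measures ANOVA. The secondary scales are analysed in the same way.
- **Planning rates (Sample Size).** The article cites "ischemic stroke recurrence rates of 12.5%-12.8% over 24 months with conventional antiplatelet therapy" and "1.7% over the same period with HH333".

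**The concern.** Recurrent stroke and death are obvious routes to a worse functional score in this population. If participants who take those routes leave assessment and their later scores become missing, the loss is related to the outcome. Under the trial's own hypothesis it is also more frequent on placebo. The functional comparison then moves towards participants who stayed free of recurrence, and the part of any functional benefit that comes from preventing strokes is diluted. The Discussion hypothesises improvement of neurological symptoms as well as prevention of recurrence, so these scales carry part of the trial's message.

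Changing to a likelihood-based repeated measures model would not by itself solve this. If post-recurrence scores are seldom observed, such a model predicts them largely from earlier scores and from participants without a recurrence.

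**Working it through.** **1. The plan's own figure.** Inputs are p₁ = 0.017, p₂ = 0.125, "a significance level (α) of 5% and a target power of 80"%, and from Statistical Analysis "All statistical analyses were two-sided with a 5% significance level". The difference is 0.108 and the mean rate 0.071.

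- Uncorrected n = [1.960 × √(2 × 0.071 × 0.929) + 0.842 × √(0.017 × 0.983 + 0.125 × 0.875)]² / 0.108² = 87.6, rounded up to 88.
- With continuity correction: (87.6/4) × [1 + √(1 + 4/(87.6 × 0.108))]² = 105.3, rounded up to 106.
- With 10% dropout: 106/0.9 = 117.8, rounded up to 118 per group.

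The stated 106 and 118 are reproduced. So 12.5% and 1.7% are the planning **recurrence** rates. They are not rates of death or dropout. The only dropout figure is 10%, not split by group.

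**2. Expected recurrences per 118.** Control: 118 × 0.125 = 14.8 (15.1 at 12.8%). HH333: 118 × 0.017 = 2.0.

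**3. Loss and dilution.** Let f be the share of recurrers who die or leave before later scores are taken (not in the article; range 0 to 1, equal in both groups). Let D be the worsening of a score caused by a recurrence. Assume that non-recurrers are alike in both groups and that those remaining are analysed.

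- Lost: p × f in each group.
- Full difference: D × (0.125 − 0.017) = 0.108 D.
- Difference among those remaining: D × [0.125(1 − f)/(1 − 0.125f) − 0.017(1 − f)/(1 − 0.017f)].

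| f | Lost, control | Lost, HH333 | Remaining difference | Share kept |
|---|---|---|---|---|
| 0 | 0% (0) | 0% (0) | 0.108 D | 100% |
| 0.25 | 3.1% (3.7) | 0.4% (0.5) | 0.084 D | 78% |
| 0.5 | 6.3% (7.4) | 0.9% (1.0) | 0.058 D | 54% |
| 0.75 | 9.4% (11.1) | 1.3% (1.5) | 0.030 D | 28% |
| 1 | 12.5% (14.8) | 1.7% (2.0) | 0 | 0% |

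Numbers of 118 are in brackets.

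**4. Size on the mRS, by assumption only.** Take D between 1 and 2 points and a standard deviation of 1 (neither is in the article). The full difference is then 0.11 to 0.22 points. Its standard error is √{[2 + D²(0.125 × 0.875 + 0.017 × 0.983)]/118}, which is 0.134 at D = 1 and 0.146 at D = 2.

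- At f = 0.5 the shortfall is 0.050 D: 0.050/0.134 = 0.4 to 0.100/0.146 = 0.7 standard errors.
- At f = 1 it is 0.108 D: 0.108/0.134 = 0.8 to 0.216/0.146 = 1.5 standard errors.

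Deaths without a recurrence would add to the loss. The article gives no mortality figure.

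**The case against.** The strongest reply is that continued assessment is the default. Table 1 keeps the scales scheduled to day 720, recurrence is not a dropout criterion, and the safety section says that unrelated adverse events are not grounds for dropout. The full analysis set keeps every score obtained before a participant leaves, including any taken after the recurrence. The article does not say whether the repeated measures ANOVA discards incomplete cases; that detail may sit in an analysis plan. The scales are exploratory, and the benefit of prevented strokes is captured by the primary endpoint.

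Most of this stands, and it limits the point to a conditional one. A reader might infer that the plan drops 12.5% of controls against 1.7% on HH333, or that the functional comparison is bound to show nothing. The documents do not support either: both follow only if every recurrer dies or leaves, and the second also needs no effect other than through recurrence. Nor do they support the reading that a recurrence ends evaluation.

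The rule itself remains. It is stated without exception, so this is not a detail left to another document. Textbox 1 joins the end of treatment to the end of evaluation and does not carry the safety section's limit for unrelated events. Interrupted dosing after a stroke could bring compliance below 80%. A death leaves scores missing whatever the dropout practice.

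**Conclusion.** The concern holds in a conditional form. Followed as written, the blanket rule makes later functional scores missing for participants who die or leave after a recurrence. At the planning rates this falls about seven times as often on controls (0.125/0.017 = 7.4) if f is equal in both groups. The upper bound is 14.8 against 2.0 of 118. Between a quarter and three quarters of recurrers lost, the recurrence-driven difference keeps 78% down to 28% of its value.

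The direction, dilution of a real benefit, rests on the trial's own rates. The size rests on f, which is unknown, and on analysis of those remaining. The exploratory scales are affected, and possibly FSS, FAS and K-PHQ-9, which fall under the same rule and analysis. The recurrence itself is still counted in the primary endpoint. This should be corrected, but it does not threaten the main conclusion.

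**What to change.** 1. In Statistical Analysis and in Analysis of Secondary Efficacy and Exploratory Endpoints, state that neither a recurrence nor the end of study medication ends the scheduled secondary and exploratory assessments. State also that these scores are collected and analysed in the full analysis set.
2. State that deaths enter the mRS comparison in the worst category of the 0 to 6 scale instead of as missing. Keep the analysis of those remaining as a sensitivity analysis. A rank or ordinal analysis at day 720 is one way to do this, but the point does not depend on it.
3. Reconcile Textbox 1, the compliance rule in Interventions and the two sentences in Safety Assessments and Monitoring, so that it is clear whether a participant with a recurrence stays under assessment. Whether treatment continues is a clinical matter on which this point takes no position.

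The cost is a few sentences, since the visits already exist in Table 1; 12 participants had been randomised at the article's last report. Sites need some extra effort to assess disabled participants, and a mean mRS that includes deaths is harder to describe.

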### Randomization, Blinding, and Allocation Concealment

A total of 236 participants who met the criteria were assigned to the HH333 or control group at a ratio of 1:1 by a statistician independent of this clinical study, using the block randomization method with R 4.4.0 (Comprehensive R Archive Network). Patients and investigators will be blinded to prevent access to the allocation results. Patients will be blinded to the study medication they are administered because they are taking either the treatment medication or a placebo. The treatment medication and placebo will be identical in size, shape, and appearance and packaged in the same type of packaging.

For allocation concealment, an independent statistician who generates the random numbers delivers a randomization code to each clinical trial site in a sealed, impermeable envelope. The investigators at each site will open the randomization envelopes in sequence in front of the patients to assign participants, and the open envelopes will be kept separate.

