### Efficacy Analysis

#### Analysis of Primary Efficacy Endpoints

The number of events will be presented for ischemic stroke recurrence during the 2-year study medication treatment period, the odds ratio of stroke recurrence will be calculated, and logistic regression analysis will be performed with ischemic stroke recurrence as the dependent variable and other factors such as HH333 treatment, risk factors, and neurological deficits as independent variables.

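### Binary logistic regression with dropouts treated as missing cannot use recurrence-free follow-up before dropout and leaves an early leaver's outcome open, so unequal dropout between arms would shift the odds ratio

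*Protocol article*

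**What the plan says.** Four parts of the protocol article bear on this point.

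- **Analysis of Primary Efficacy Endpoints:** an odds ratio is calculated for recurrence during the 2-year treatment period, and "logistic regression analysis will be performed with ischemic stroke recurrence as the dependent variable". Time to recurrence does not appear.
- **Statistical Analysis:** if values are missing or "participants are dropped before the end of the study, the data will be treated as missing data". The same paragraph makes the full analysis set the main set for efficacy. It admits anyone with one post-dose assessment of the primary outcome and says that all of their data are included.
- **Primary Endpoint:** recurrence is checked at ten scheduled points from day 30 to day 750.
- **Sample Size:** "the sample size was 106 patients per group and 212 patients in total at 2 years", after which "a dropout rate of 10% was considered", giving 118 per group. No dropout rate is given by arm.

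The dropout criteria (Textbox 1) and Interventions list routes out of the study that include compliance below 80%, and adverse events or comorbidities.

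**The concern.** Recurrence is an event that happens at some time during about two years, and the design checks for it repeatedly. A yes/no model has no place for partial follow-up. A participant who leaves recurrence-free at day 600 has no 2-year outcome, while one who recurs at day 100 does. The stated rule then allows at least three codings for early leavers:

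- **A:** recurrences seen before dropout count, and recurrence-free leavers are missing.
- **B:** recurrence-free leavers are coded as having no recurrence.
- **C:** all outcome data of leavers are set aside, including recurrences already seen.

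A overstates the risk in the arm with more dropout, and B understates it. The primary estimate could therefore turn on a coding choice made after the data are in. Compliance and adverse events over 720 days of daily dosing are plausible reasons for dropout to differ between HH333 and placebo.

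**Working it through.** **1. The plan's own figure.** Inputs from Sample Size: "control group (P_2_=0.125-0.128), HH333 group (P_1_=0.017", α 5%, power 80%. Two-sided testing comes from Statistical Analysis ("All statistical analyses were two-sided with a 5% significance level"), and 1:1 allocation from the randomization section. With mean risk 0.071 and difference 0.108:

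- Uncorrected: n = [1.96·√(2·0.071·0.929) + 0.8416·√(0.017·0.983 + 0.125·0.875)]² / 0.108² = 87.6, so 88.
- With continuity correction: (87.6/4)·[1 + √(1 + 4/(87.6·0.108))]² = 105.3, so 106.
- Dropout: 106/0.90 = 117.8, so 118.

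The stated 106 and 118 are reproduced. The 10% allowance already pays for lost outcomes.

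**2. Model for dropout.** Assumptions not in the document: constant hazards, dropout unrelated to prognosis, and the arm-specific rates. For 2-year risk p and dropout d, put λ = −ln(1−p) and μ = −ln(1−d). Then:

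- recurrence-free completers: C = (1−p)(1−d)
- recurrences seen before dropout: E = [λ/(λ+μ)]·(1−C)
- odds under coding A: E/C
- odds under coding B: E/(1−E)

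**3. No true effect, p = 0.125 in both arms (λ = 0.1335).**

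| Dropout | μ | C | E | Odds A | Odds B |
|---|---|---|---|---|---|
| 10% | 0.1054 | 0.7875 | 0.1188 | 0.1508 | 0.1348 |
| 20% | 0.2231 | 0.7000 | 0.1123 | 0.1605 | 0.1265 |
| 30% | 0.3567 | 0.6125 | 0.1056 | 0.1723 | 0.1180 |

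Odds ratios, HH333 against control:

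| Dropout HH333 / control | A | B |
|---|---|---|
| 10% / 10% | 1.00 | 1.00 |
| 20% / 10% | 1.06 | 0.94 |
| 30% / 10% | 1.14 | 0.88 |
| 10% / 30% | 0.875 | 1.14 |

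**4. With a true effect.** For 6.25% against 12.5%, the true odds ratio is (0.0625/0.9375)/(0.125/0.875) = 0.47. At 30%/10% dropout it becomes 0.53 under A and 0.41 under B. At the planning rates with 10%/10% dropout, the odds ratio under A is 0.999 of its true value, and about 5% of person-time belongs to recurrence-free leavers and is unused.

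**5. Coding C.** There is no bias if dropout is unrelated to prognosis. If leavers are assumed to have 2 to 3 times the recurrence risk, the odds ratio at the planning rates is multiplied by 0.93 to 0.87 (20%/10%) or 1.12 to 1.21 (10%/20%).

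**6. Operating characteristics.** Simulation with 6,000 runs and 118 per group, using an unadjusted chi-square test as a stand-in for the logistic model:

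| Scenario | Binary A | Binary B | Binary C | Log-rank |
|---|---|---|---|---|
| Power at planning rates, 10%/10% dropout | 0.92 | 0.92 | 0.90 | 0.92 |
| Type I error at 12.5% risk, 30%/10% dropout | 0.066 | 0.062 | 0.052 | 0.051 |

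**7. Events.** At the planning rates with 10% dropout, control gives 118·0.1188 = 14.0 and HH333 gives 118·0.0161 = 1.9, about 16 in total. The design hazard ratio is ln(0.983)/ln(0.875) = 0.128. The Schoenfeld formula asks for 8 events and Freedman's for 14, so a time-to-event analysis needs no larger sample.

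**The case against.** A fixed 2-year binary endpoint with an odds ratio is a recognised choice and matches the two-proportion sample size. The only documented dropout rate is 10% without an arm split, and at equal rates the estimate is essentially unbiased. Even with unequal dropout the shift is small against sampling error. With 106 evaluable per group, the standard error of the log odds ratio is about 0.81 at the planning rates and 0.50 at 6.25% against 12.5%, while ln 1.06 = 0.06 and ln 1.14 = 0.13. All of this stands, and it limits how serious the point is. It does not settle how an early leaver is coded, and it is no reason to keep a method that discards follow-up when a better one uses the same visits.

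A further objection also stands: censoring at last contact assumes that dropout is non-informative, so a log-rank or Cox analysis does not remove bias from compliance-driven or adverse-event-driven dropout.

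Three stronger readings are tempting, but the document does not support them:

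- *The odds ratio reflects dropout rather than HH333.* A true 0.47 moves only to 0.53 or 0.41 in the extreme case, so treatment still drives the estimate.
- *Someone who recurs and then leaves is certainly set to missing.* The rule can be read so, but the full analysis set wording points towards counting that recurrence.
- *Deaths and haemorrhagic strokes are simply missing.* No such rule is stated. Haemorrhagic events are collected as safety data, and haemorrhagic stroke is not itself a listed dropout criterion.

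**Conclusion.** The point holds as a should-fix. The article itself fixes both the binary model and the missing-data rule, so this is not detail left to an analysis plan. Together they make recurrence-free follow-up before dropout unusable, and they leave the early leaver's outcome undefined within the main analysis set.

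The bias is conditional. When recurrences seen before dropout are counted, it needs dropout to differ by arm. It is then about 6% on the odds ratio for 20% against 10%, and 12% to 14% for 30% against 10%, with the direction set by the coding. Those rates and the constant hazards are assumptions. At 10% in both arms the cost is about 5% of person-time, with essentially no bias and little effect on power. With only about 16 expected events, however, a few recoded outcomes could matter.

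**What to change.** Before unblinding:

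1. In Analysis of Primary Efficacy Endpoints, make the primary analysis time from randomisation to first recurrent ischemic stroke, with Kaplan-Meier curves, a log-rank test and a Cox hazard ratio, censored at last contact. Treat death as a competing event in a supporting cumulative-incidence analysis. Keep the odds ratio as a secondary summary, with its coding of early leavers stated.
2. In Statistical Analysis, limit the missing-data rule to time after last contact, so that recurrences and follow-up seen before dropout always count.
3. Add a sensitivity analysis for missing outcomes that varies the recurrence risk after dropout by arm, because the compliance and adverse-event routes may be informative.

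Cost: changed analysis wording, and recording the dates of recurrence and last contact. No extra patients or visits are needed. The drawback is that the headline measure changes from an odds ratio to a hazard ratio. The timing is favourable: the Results section reports 12 participants randomized by November 13, 2024, and no data analysed.

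### The per-protocol set requires completion of the study, so a participant whose recurrent stroke is fatal or ends participation leaves the supportive recurrence comparison with an observed primary event

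*Protocol article*

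**What the plan says.** All of the following is in the protocol article.

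- **Main set (Statistical Analysis).** "Efficacy analysis will be conducted using the results of the full analysis set as the main analysis". Membership needs one assessment after dosing, not completion: "The full analysis set includes all data from participants with at least one efficacy assessment at the primary outcome after taking the study medication".
- **Per-protocol set (same section).** "The per-protocol set included participants who were eligible for full analysis and successfully completed the study". Its purpose is stated: "a per-protocol set analysis will be conducted separately to evaluate whether there are differences from the full analysis set results". Completion is not defined further.
- **Dropout (Textbox 1).** One ground is that, in the investigator's judgment, "the patient is no longer able to participate in the study because of adverse events or comorbidities". The consequence is that "the researcher may stop the treatment and evaluation and drop the participant". Compliance below 80% is another ground, and the Interventions section applies it at any time during the study.
- **Safety Assessments and Monitoring.** Two statements pull in different directions. Adverse events not related to the study medication are not grounds for dropout. A serious adverse event, however, leads to an immediate stop of the study, partial or total.
- **Primary endpoint and analysis.** The endpoint is recurrent ischemic stroke within 750 days. It is analysed as a yes/no outcome by logistic regression, with an odds ratio.

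**The concern.** Per-protocol membership depends on a state reached after randomization, and the primary outcome can itself prevent that state. A fatal recurrence cannot be followed by completion. A disabling one can lead to dropout for an adverse event, or to compliance below 80% through missed doses. It might also fall under the stop for serious adverse events, if a partial stop means the affected participant. The article's Introduction says that recurrent stroke carries twice the risk of death and worse function than a first stroke, so such cases are foreseeable.

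These participants' binary outcome is fully known: they had the event. Removing them is therefore not a matter of missing information. A per-protocol result that differs from the main result could then reflect deleted strokes rather than adherence, and adherence is what the comparison is meant to examine.

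**Working it through.** **Inputs from the article (Sample Size, Statistical Analysis).** Two-year recurrence 0.125 to 0.128 in control and 0.017 with HH333; two-sided 5% level; 80% power; 106 per arm, raised to 118 for 10% dropout.

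**Input that is assumed.** f, the share of participants with a recurrence who do not complete. The article gives no figure, so a range is shown.

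**Step 1: reproduce the plan's figure.** With p1 = 0.017, p2 = 0.125, mean 0.071 and d = 0.108:

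- Uncorrected n = [1.96·√(2·0.071·0.929) + 0.842·√(0.017·0.983 + 0.125·0.875)]² / 0.108² = 87.6, so 88.
- With continuity correction, n/4·[1 + √(1 + 4/(n·d))]² gives 106, as stated.
- 106/0.9 = 117.8, so 118, as stated.

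**Step 2: expected events at 106 per arm.** HH333: 106 × 0.017 = 1.8. Control: 106 × 0.125 = 13.3 (13.6 at 0.128). The total is about 15.

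**Step 3: apply the completion rule.** In each arm the events kept are n·p·(1−f), the set size is n − n·p·f, and the rate is their quotient. For f = 0.5:

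- HH333: 0.90/(106 − 0.90) = 0.9%.
- Control: 6.62/(106 − 6.62) = 6.7%.

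Power is the normal approximation for two proportions with pooled null variance and no continuity correction: Φ{[d − 1.96·SE0]/SE1}. At f = 0, SE0 = √(0.071·0.929·2/106) = 0.0353 and SE1 = √(0.1261/106) = 0.0345. This gives Φ(1.13) = 0.87.

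| f, same in both arms | Events HH333 / control | Rates | Difference (points) | Power |
|---|---|---|---|---|
| 0 | 1.8 / 13.3 | 1.7% / 12.5% | 10.8 | 87% |
| 0.25 | 1.4 / 9.9 | 1.3% / 9.7% | 8.4 | 76% |
| 0.5 | 0.9 / 6.6 | 0.9% / 6.7% | 5.8 | 60% |
| 0.75 | 0.5 / 3.3 | 0.4% / 3.4% | 3.0 | 35% |
| 1 | 0 / 0 | 0 / 0 | 0 | not estimable |

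With a control rate of 0.128, power for f = 0 to 0.75 is 88%, 78%, 61% and 36%.

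**Step 4: the odds ratio.** The odds in an arm are n·p·(1−f)/[n·(1−p)], so each arm's odds are multiplied by (1−f). The odds ratio (HH333 against control) is multiplied by (1−f_HH333)/(1−f_control). With equal f this factor is 1, and the control-to-HH333 odds ratio stays at about 8.3 (8.5 at 0.128). It moves only if f differs between arms.

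**Step 5: sparseness.** Even with equal f, the HH333 arm may keep no event at all. The chance is (1 − 0.017)^106 = 0.16 at f = 0 and (1 − 0.0085)^106 = 0.40 at f = 0.5. An ordinary logistic model then gives no finite estimate of the odds ratio.

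**The case against.** The strongest reply is that the main analysis does not use this rule, and that the route to exclusion is less certain than it looks.

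- **Recurrence is not a listed dropout criterion**, and the safety section says that adverse events unrelated to the study medication do not lead to dropout. A recurrence judged unrelated might therefore not end participation. This stands: f may be small. It does not cover a fatal recurrence or the compliance rule, and it sits uneasily beside the stop for serious adverse events.
- **Event-free participants also leave the set**, through withdrawal, loss to follow-up, low compliance or other adverse events. This stands. Only the exclusions triggered by a recurrence are specific to participants with events.
- **The analysis uses the odds ratio**, which equal f leaves unchanged in expectation. This stands. In a double-blind trial nothing in the article suggests a particular difference in f between arms. With 1.8 expected HH333 events, a change in f of 0.3 in that arm is about half a participant.
- **The power figures are a gauge, not a design failure.** The 87% omits the continuity correction behind the plan's 106 at 80% power. The 106 is also already net of the 10% dropout, so removing more non-completers partly counts dropout twice. Both points stand. The proportional loss of events is the same from any starting size.
- **Completion could be defined in a fuller document.** That is possible. But the article does more than stay silent: it states a membership rule which, as worded, depends on the outcome.

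A reader might also infer that a recurrence could lead to exclusion by reclassifying the stroke mechanism, under "Found not to meet inclusion or exclusion criteria after screening". The documents do not support this. The inclusion criterion concerns the index stroke within 90 days of screening, a later stroke of another type does not breach it, and no reclassification step is described.

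**Conclusion.** The point holds as a defect in the supportive analysis. Taken literally, the completion rule removes participants whose recurrence is fatal or ends participation, although their primary outcome is known. With about 15 expected events, this lowers the per-protocol recurrence rates and thins the comparison quickly: half the events are lost at f = 0.5. The size rests on the plan's own recurrence rates and on an assumed f, for which the article gives no value.

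Two stronger readings are tempting and not supported:

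- **That the main result is compromised.** The full analysis set does not require completion. The separate sentence that when "participants are dropped before the end of the study, the data will be treated as missing data" does not say that a recurrence already recorded is discarded, and this point does not rest on it.
- **That the per-protocol odds ratio is biased.** That needs f to differ between arms, and nothing in the article shows that it would.

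The change is worth making, but it is not critical to the primary conclusion.

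**What to change.** Replace the completion condition with a definition along these lines: *the per-protocol set comprises members of the full analysis set who met the eligibility criteria, were adherent and had no major protocol deviation up to the first recurrent ischemic stroke or the end of scheduled follow-up, whichever came first. A participant with a recurrence is complete for the primary endpoint at that date and remains in the set as an event, whatever happens to participation afterwards.* The article does not define major deviations, so they should be listed before unblinding.

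Separately, the dropout criteria and the two statements in the safety section (unrelated adverse events, and the stop for serious adverse events) should be reconciled so that it is clear when a recurrence ends participation. This review takes no position on which clinical rule is right.

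The cost is a short text change with no added patients or visits. At the date reported (13 November 2024), 12 participants had been randomized and no analysis had been done. The downside is that some per-protocol participants will lack later scale scores, so the secondary and exploratory per-protocol analyses will have more missing values.
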